#### Randomisation and masking

Once consented, participants will be randomised using a third-party web-based randomisation system which will ensure concealed allocation. Participants will be stratified according to the number of previous detoxifications (> 2 vs ≤ 2) and site. Randomisation will have a random block size [2–4]. Research assistants will be blind to the randomisation of the opposite study site and will conduct those follow-up interviews. Any breach in blinding/unmasking, a common problem with single-blind trials, will be monitored by asking the research assistants to report any such incident, to ensure that the research assistants are not aware, as far as possible, to which group the individual was allocated in the opposing study site.

#### Treatment fidelity

Twenty-five percent of the intervention sessions, offered across both recruitment sites, during the whole duration of the study recruitment and treatment stage, will be observed and rated using the Yale Adherence and Competence Scale (YACS II) (2005) [27]. This is a validated instrument measuring the use of CBT techniques. The tool can be adapted to the focus of the therapy under investigation. Furthermore, 10% of the sessions will be observed and rated by an additional independent rater using YACS II. Group facilitators will complete a self-assessment form following each session to reflect on their fidelity to the intervention manual.

Twenty-five percent of the key-working sessions offered to the control group will be audio recorded and be rated to assess possible contamination between the study arms using a specifically developed form based on YACS II items as well as the main objectives of the SPADe group intervention. Ten percent of those sessions will also be independently rated.

#### Statistical analysis

The main analysis will be based on the intention-to-treat principle considering all randomised clients according to the arm they were allocated. As the trial is a feasibility study, the main analysis is to be descriptive and estimate the potential effect sizes and parameters required for the sample size calculation, rather than formal hypothesis testing.

The feasibility outcomes will be summarised using descriptive statistics where appropriate. The potential primary and secondary outcomes will be summarised by arm, as well as completion rates estimated for each outcome measure. Duration of continuous abstinence, as measured from randomisation, and the time to relapse, as measured from the end of the intervention, will be analysed using a Kaplan-Meier curve and log-rank test. The percentage of days of abstinence (PDA) will be analysed using a regression model. Formal hypothesis tests and confidence intervals will be conducted although due to the nature of this trial, they will be treated cautiously and the main focus will be on the completion rate of outcomes and the estimation of parameters required for a sample size calculation for the main trial.

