**Methods:**

The study corresponds to phase 2 of the Medical Research Council (MRC) complex interventions guidelines which cover the development and feasibility testing of an intervention. The work is in three stages. The development, adaptation and implementation of the Structured Preparation before Alcohol Detoxification (SPADe) intervention (stage 1), a randomised feasibility study with economic evaluation (stage 2) and a qualitative study (stage 3). Fifty participants will be recruited from two community alcohol treatment services in England. Participants will be randomised in two arms: the treatment as usual arm (TAU), which includes planned medically assisted detoxification and aftercare and the intervention arm in which participants will receive structured group preparation before detoxification in addition to TAU. The main outcomes are duration of continuous abstinence with no incidents of lapse or relapse, percentage of days abstinent and time to relapse.

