In the light of the abovementioned evidence indicating the potential risk of an accumulation of adverse effects following repeated detoxifications, and until definitive evidence is generated to confirm or refute a causal relationship, it is prudent to maximise treatment effectiveness and to reduce the risk of exposing people to repeated detoxifications and the potential adverse effects associated with the detoxification process itself. Although the existing evidence is only indicative, it is possible that the long-term course, and economic and social impact of alcohol dependence, is not only due to the natural process of the phenomenon, but is also associated with the existing treatment approach that emphasises the importance of the provision of detoxification per se, without any emphasis on long-term sustainable outcomes. There is currently no guidance specifically on preparation for the detoxification process, apart from general guidance on care coordination and case management [4]. Absence of specific guidance reflects the lack of developed interventions in this area. Evidence is required on whether structured preparation before detoxification rather than detoxification alone improves treatment outcomes and therefore whether the whole treatment paradigm should shift. Before embarking on a full trial of the effectiveness of such structured preparation, there is a need to undertake a feasibility study to establish key parameters that influence trial design such as recruitment, adherence to the intervention, retention and sensitivity of alternative outcome measures.

A literature search of PubMed Central using alcohol relapse prevention, treatment-related MeSH terms undertaken in June 2014 found (1) that group interventions with diverse theoretical bases are considered to be more cost-effective than one-to-one interventions [13] and (2) cognitive behaviour therapy (CBT) relapse prevention interventions are well-supported by evidence [14].

In the UK, an innovative group intervention for preparation before alcohol detoxification, based on CBT relapse prevention interventions, developed by members of the research team, reduced detox dropouts [15] and improved outcomes at 1, 3 [5] and 6 months [16]. However, these findings were from small naturalistic studies. Qualitative evidence found that ‘regaining control’ was the main learning point across all group sessions of the programme [17].

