#### Participants

We will recruit 50 alcohol-dependent participants, aged 18 or over who have a desire to stop drinking. As both recruiting services operate within a multi-lingual, multi-faith and multi-cultural environment, we will provide study information in the two most prevalent languages spoken by non-English speakers in our locations, in addition to the material in English. Should we recruit any non-English speaking participants to the intervention arm, the sessions will be provided in one-to one format by the intervention group facilitator, with the support of an interpreter if required. Participant flow to the study is shown in Fig. 1. We will aim to recruit at least one of the above participants in the qualitative study to explore their experience.

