#### Outcome measures

Feasibility outcomes will be (1) Recruitment and retention rates: we will monitor (monthly) the number of alcohol-dependent clients accessing services during the recruitment period of the study, how many meet the eligibility criteria and how many were invited and accepted into the study and retained in each group for the full 12 months. (2) Compliance with treatment: number of SPADe sessions attended (for the intervention arm) using the facilitator’s record of attendance. (3) Data collection and completeness: attendance for assessments and completeness of instruments; loss to follow-up and missing data for all outcomes will be analysed.

A variety of possible outcomes will be used, assessed at different time points (3, 6 and 12 months following randomisation), so the primary outcome for the main trial can be identified and sample size calculations conducted, including duration of continuous abstinence with no incidents of lapse or relapse; percentage of days of abstinence (PDA) (both self-report using Timeline Followback method (TLFB)) [22]; and time to relapse (from stopping alcohol to first day of alcohol use, also as defined by self-report).

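### Effect sizes observed in 50 participants should not set the main trial's target difference or guide the choice of its primary outcome

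*Protocol article*

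**What the plan says.** Sample size: "We will recruit 50 alcohol-dependent participants" (Participants). The Abstract adds that "Participants will be randomised in two arms", without giving the ratio.

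Candidate primaries: "The main outcomes are duration of continuous abstinence with no incidents of lapse or relapse, percentage of days abstinent and time to relapse" (Abstract, Methods). The Outcome measures section has them "assessed at different time points (3, 6 and 12 months following randomisation), so the primary outcome for the main trial can be identified" and the sample size worked out. The Background lists, among the design parameters to be established, "retention and sensitivity of alternative outcome measures".

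Use of the results: the Statistical analysis section says the main analysis is to "estimate the potential effect sizes and parameters required for the sample size calculation, rather than formal hypothesis testing". It assigns a Kaplan-Meier curve and log-rank test to continuous abstinence and to time to relapse, and a regression model to percentage of days abstinent. It then states: "Formal hypothesis tests and confidence intervals will be conducted". The rest of that sentence says these will be read with caution, and that the main focus is outcome completion and the parameters needed for sizing.

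The Discussion gives its own list of what will inform the main trial's size: numbers eligible, recruitment, loss to follow-up, adherence and the SD of the primary outcome measures. That list contains no effect size.

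**The concern.** A sample size calculation needs two kinds of input. Nuisance quantities, such as the SD, event rate, correlation and attrition, can reasonably be estimated from a feasibility study. The target difference is a judgement about what effect would matter, and a study of 50 people cannot estimate it usefully. The Statistical analysis section puts effect sizes and the other parameters together as things to be estimated here for the sizing.

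The design of the main trial is what this study exists to deliver. If its observed effect becomes the target difference, sampling error passes straight into the main trial's size. A chance overestimate gives a trial that is too small, and a chance underestimate may mean that no trial is run. The trials that go ahead therefore tend to be the underpowered ones. A second route opens if the same contrasts help decide which outcome becomes primary, because a contrast picked for being large is biased upwards.

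**Working it through.** **Inputs from the article.** N = 50; two arms; three candidate outcomes; follow-up at 3, 6 and 12 months. The article gives no effect size, SD, alpha or power, so there is no figure of its own to reproduce.

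**Assumptions.** 1:1 allocation, so 25 per arm, or 20 per arm to allow for loss. Main trial sized at two-sided 5% and 80% power. True effects of 0.3 and 0.5 SD, for illustration. Effects are expressed as standardised differences so that the outcomes share a scale.

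**Step 1: precision.** SE = √(2/n per arm).
- 25 per arm: √(2/25) = 0.283; 95% half-width 1.96 × 0.283 = 0.55 SD.
- 20 per arm: √(2/20) = 0.316; half-width 0.62 SD.
- For the time-to-event outcomes, the approximate 95% limits of a hazard ratio are the estimate multiplied and divided by exp(1.96 × 2/√events): 2.05 with 30 events, 1.74 with 50.

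An observed 0.3 SD at 25 per arm would be compatible with anything from −0.25 to 0.85 SD.

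**Step 2: power of the tests in this study.** At 25 per arm, power is 18% for 0.3 SD and 42% for 0.5 SD. Reaching 80% needs a true effect of about 0.79 SD.

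**Step 3: sizing on the observed effect, one pre-chosen outcome.** n per arm = 2 × ((1.96 + 0.84)/observed effect)².

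One case: the truth is 0.3 SD and the study shows 0.5 SD. Then n = 63 per arm, and true power is Φ(0.3 × √(63/2) − 1.96) = Φ(−0.28), about 39%. A target of 0.3 SD would have needed 175 per arm.

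Over repeated feasibility studies (simulation, 25 per arm, main-trial n rounded up, observed effects of 0.1 SD or less treated as not proceeding):

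| True effect | Mean true power | Runs below 80% |
|---|---|---|
| 0.3 SD | 61% | 66% |
| 0.5 SD | 72% | 54% |

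The last column can be checked directly. Power is below 80% whenever the observed effect exceeds the true one, which has probability 0.5. Dividing by the chance of proceeding gives 0.5/0.760 = 66% and 0.5/0.922 = 54%.

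**Step 4: if the contrast also influenced the choice of primary.** The Statistical analysis section describes one survival analysis for each of the two time-to-event outcomes. Percentage of days abstinent could be compared at three visits. That makes 1 + 1 + 3 = 5 contrasts. If the largest of five were used for sizing, mean true power at a true 0.3 SD would be about 48% to 53% for between-contrast correlations of 0.7 to 0.9.

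**Step 5: what 50 participants can supply.** A within-arm SD on 48 degrees of freedom has 95% limits of about 0.83 to 1.25 times the estimate. That is usable for sizing if the upper limit is carried forward.

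**The case against.** The best reply is that the article never says the point estimate becomes the target difference. The closing sentence of the Statistical analysis section speaks only of parameters. The Discussion's list of sizing inputs omits the effect size, and the planned confidence intervals would show the imprecision. The main trial's target difference also belongs to a later protocol, so its absence here is no fault. This stands in part: the consequence has to be stated conditionally. It does not remove the point, because the statement of the main analysis names effect sizes among the quantities to be estimated for sizing, and that wording should agree with the Discussion's list.

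Four stronger readings are tempting, and the article does not support them.

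- **The primary will be the outcome and visit with the largest effect out of nine.** No such rule appears. The article also names completion, acceptability and response rates, and its use of sensitivity is undefined. Three outcomes at three visits is an upper bound; the described analyses give about five contrasts.
- **The main trial would be underpowered.** This holds only if the observed effect is used as the target, and even then as a likelihood: in Step 3, 34% (100 − 66) and 46% (100 − 54) of the runs that proceed reach 80%.
- **The results invite a false decision on whether to proceed.** No progression rule based on an effect or a p-value is given.
- **The section renounces tests and then performs them.** It calls the main analysis descriptive and asks for the tests to be read with caution. The two sentences sit awkwardly together, but no confirmatory claim is made.

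**Conclusion.** The point holds in conditional form. The article makes effect sizes from 50 participants an input to the main trial's sample size and identifies the primary outcome from the same data. The estimates are too imprecise for the first use: ±0.55 SD at 25 per arm, ±0.62 SD at 20. If the observed effect is taken as the target, the loss is material without any selection among outcomes, at roughly 19 percentage points of mean power for a true 0.3 SD (80 − 61) and 8 for a true 0.5 SD (80 − 72).

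The further loss in Step 4 depends on the contrast influencing the choice of primary, which the article neither states nor excludes. All the power figures rest on the assumed true effects, 1:1 allocation, an 80% target and the 0.1 SD cut-off for not proceeding. The confidence interval widths rest only on the numbers per arm.

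**What to change.** In the Statistical analysis section, replace the clause on estimating effect sizes and parameters for sizing with wording such as:

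*The main trial's target difference will be a pre-specified important difference and will not be taken from the effect observed in this study. This study will supply the SD with its confidence limit, the control-arm event rate, correlations between repeated measures, completion and retention. Between-arm estimates will be reported with confidence intervals, only to check that the target difference is plausible.*

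In the Outcome measures section, add that the primary will be chosen on completeness, acceptability, distribution and relevance, and not on the observed between-arm contrast.

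Label the log-rank and regression tests as exploratory, with no part in choosing the primary or sizing the main trial. They need not be deleted.

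The change is wording only and needs no further data or participants. Its cost is that the main trial's sample size may come out larger than one based on a favourable observed effect.

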#### Inclusion criteria

Inclusion criteria are as follows:Presentation to either of the two alcohol services seeking abstinence from alcohol.Alcohol dependence (moderate to severe), scoring 16 and above on Severity of Alcohol Dependence Questionnaire (SADQ) (see the ‘Outcome measures’ section below). This level of dependence indicates that it would be clinically appropriate to receive a medically assisted detoxification [4].Stated intention to stay in the area within the time period of the intervention.Willingness to be part of a group intervention if randomised to receive it.

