#### Trial arms

##### Treatment as usual

Usual detoxification/control comprises planning for detoxification, detoxification delivery and aftercare. Standardised procedures across sites will be confirmed in phase 1. Service users enter detoxification at the first available opportunity (likely to be within 4 weeks from presentation). Whilst waiting for detoxification, they will meet their key worker (one-to-one) on 3–4 occasions to maintain motivation and plan aftercare.

Detoxification is medically assisted in the community as an outpatient, or inpatient, as clinically indicated. The choice depends on health risk factors and availability of social support during detoxification. The type of detoxification has been shown by NICE not to affect treatment outcomes [4]. Aftercare (following detoxification) includes peer support groups such as Self-Management and Recovery Training (SMART) Recovery or Alcoholics Anonymous (AA), a small number of individual key worker sessions, pharmacological interventions as appropriate or more comprehensive aftercare group programme. Participants in both intervention and control groups will receive all the above elements of usual care available in the recruiting service. Each participant’s care pathway will be recorded in detail and analysed for variability within and between sites as part of the economic evaluation (see below), to ensure these are equivalent across trial arms.

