##### Intervention

The intervention provides structured group preparation (additional to usual care) with the aim of helping participants regain control over their drinking, prior to detoxification. Part of this control is lifestyle modification, which is necessary for maintaining abstinence post detoxification. Regaining control is linked with developing new coping skills and enhanced self-efficacy.

The six sessions are numbered and offered weekly in a given order. Stabilisation of the amount and pattern of drinking is a common theme across all the sessions. To that effect, each session can act as an entry point (i.e. an open rolling programme group), despite the special theme covered in depth during the second part. Each session has two facilitators, lasts for 1 h and is divided into three parts:In the first part (15 min), group rules are established (as advised in PPI meetings), new members are introduced, aims of the intervention, in-between sessions practice allocated in previous session reviewed as are individual targets set for the previous week are reviewed.The second part (30 min, main part) explores the following themes depending on the session number: 1—understanding habit, addiction and alcohol dependence; 2—stabilise and control your drinking; 3—lifestyle changes for you and the people around you; 4—reduction of your drinking; 5—achieving abstinence; and 6—relapse prevention strategies.In the third part (15 min), the group summarises the main learning points and agrees in-between sessions practice and targets to be achieved before the next session. A group work folder will be provided enabling notes and worksheets to be kept together, as also suggested by PPI meetings.

The number of participants per group at any point is between two and eight, as this is considered appropriate for theory-based treatment groups, to reach a balance between education, treatment, group interactions and facilitator’s attention to each participant [13]. This maximum is unlikely to be reached in the feasibility trial. If only one participant is present, the session will be offered by one of the facilitators as an individual session. The duration of 1 h as suggested in PPI, will reduce risk of withdrawal symptoms and help participants to maintain concentration.

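### Continuous abstinence is timed from randomisation, before detoxification, so the outcome is either uninformative or distorted by how long each arm waits to detoxify

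*Protocol article*

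**What the plan says.** All references are to the Protocol article.

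- **Outcome.** The Outcome measures section lists "duration of continuous abstinence with no incidents of lapse or relapse" first among the outcomes from which the main trial's primary will be chosen. It gives this outcome no start date. It starts the companion outcome, time to relapse, at stopping alcohol.
- **Time origin and method.** The Statistical analysis section supplies the origin: "Duration of continuous abstinence, as measured from randomisation". This outcome and time to relapse "will be analysed using a Kaplan-Meier curve and log-rank test". The same sentence starts time to relapse at the end of the intervention, which differs from the Outcome measures section and is a date that the usual-care arm does not have.
- **Who is randomised, and when.** Eligibility requires "Alcohol dependence (moderate to severe), scoring 16 and above on Severity of Alcohol Dependence Questionnaire (SADQ"), and the Participants section describes people "aged 18 or over who have a desire to stop drinking". They are approached on entering the service, and "Once consented, participants will be randomised using a third-party web-based randomisation system". Detoxification is still to come in both arms.
- **Usual care.** "Service users enter detoxification at the first available opportunity (likely to be within 4 weeks from presentation").
- **SPADe.** "The six sessions are numbered and offered weekly in a given order". The sessions are delivered before detoxification, and stabilising the amount and pattern of drinking runs through all of them.

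**The concern.** A Kaplan-Meier analysis needs a time zero at which participants are in the state being timed. Here time zero falls before abstinence is expected to have begun, and the interval between the two is expected to differ by arm because SPADe is placed in front of detoxification. The article does not say how drinking between randomisation and detoxification is to be treated.

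The study exists to compare candidate outcomes and to supply effect sizes and other parameters for the main trial's sample size. If this candidate is computed as worded, it may look useless because of its origin, or it may show an arm difference produced by waiting time. Either result could mislead the choice of primary outcome or the size of the next trial.

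**Working it through.** The article gives no power or event figure for this outcome, so there is nothing to reproduce. The check sets out what each reading of the text implies.

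**Inputs from the article:** usual-care detoxification likely within 4 weeks of presentation (taken as day 28); six weekly SPADe sessions, which span five intervals (5 × 7 = 35 days) or six weeks (6 × 7 = 42 days); 50 participants; follow-up to 12 months.

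**Assumptions:** 1:1 allocation (25 per arm); SPADe detoxification at day 35 or day 42, counted like the usual-care date from a common zero; time from detoxification to first drink exponential with median 30, 60 or 120 days, identical in both arms.

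**Reading 1: any drink after randomisation is the event.** People still drinking at randomisation fail at or near day 0 in both arms. There is no bias between arms, but almost no information either.

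**Reading 2: time from randomisation to the first drink after detoxification.** For each participant T = D + X, where D is the day of detoxification and X is exponential with rate ln 2 / median. T is censored at day 365. The waiting time D counts as event-free. With no true effect the medians from randomisation are simply shifted:

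| Post-detoxification median | Usual care (D = 28) | SPADe (D = 35) | SPADe (D = 42) |
|---|---|---|---|
| 30 days | 28 + 30 = 58 | 35 + 30 = 65 | 42 + 30 = 72 |
| 60 days | 88 | 95 | 102 |
| 120 days | 148 | 155 | 162 |

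Simulating this, with the hazard ratio (HR) approximated by exp((O − E)/V) from the log-rank statistic, gives:

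| Gap | Post-detoxification median | Apparent HR | Log-rank falsely favours SPADe (nominal 2.5%) |
|---|---|---|---|
| 7 days (28 vs 35) | 30 / 60 / 120 days | about 0.85 / 0.92 / 0.96 | about 8% / 5% / 3% |
| 14 days (28 vs 42) | 30 / 60 / 120 days | about 0.70 / 0.85 / 0.90 | about 21% / 9% / 6% |

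A larger check, with 20,000 simulated trials per cell, gave 0.84, 0.92 and 0.95 (9%, 5%, 4%) for the 7-day gap and 0.71, 0.84 and 0.91 (21%, 9%, 5%) for the 14-day gap. With no gap the HR was 1.00 and the false-favour rate 2.7%, so the excess comes from the gap.

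**Reading 3: length of the abstinent spell inside a window fixed at randomisation.** The longest possible spell is the window minus the time to detoxification. By a 13-week visit that is 13 − 4 = 9 weeks in usual care, against 13 − 5 = 8 or 13 − 6 = 7 weeks in SPADe. By 52 weeks it is 48 against 47 or 46. The distortion now runs against SPADe.

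**With the clock started at stopping alcohol,** D drops out of T. Identical relapse after stopping then gives no expected difference between arms.

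**The case against.** Several points on the other side are fair.

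- **The premises are partly inferred.** No section says that every participant is drinking at randomisation, and none gives a detoxification date for SPADe. The 4 weeks are only likely and run from presentation, which precedes randomisation. SPADe is an open rolling group, and the article does not say that all six sessions must be finished before detoxification. A later SPADe detoxification is therefore expected, but its size is unknown. A reader might infer that everyone is drinking, or that a delay of fixed length is built in; the text supports neither.
- **The direction is not settled.** A reader might infer that the stated origin must flatter SPADe. Reading 3 goes the other way, and assessment at 3, 6 and 12 months gives it some support, although the Kaplan-Meier wording makes it less natural.
- **Extreme figures need extreme assumptions.** With detoxification at days 14–28 against 42–56 and a 30-day median, the false-favour rate reaches 54%. That average gap of 28 days appears nowhere in the article, so the figure should not be quoted as the expected size.
- **This is a feasibility study.** The analysis is mainly descriptive, tests are to be read cautiously, and this is one of three candidates. Percentage of days abstinent needs no start of abstinence.

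The last point lowers the stakes but does not remove the defect: caution about p-values does not correct a displaced estimate, and estimating effect sizes is a stated purpose. Nor does intention to treat require this origin. That principle governs who is compared, and it is kept if never-abstinent participants are scored 0. Finally, this is not detail left to a later document, because the article has stated the origin.

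**Conclusion.** The point holds. Measuring continuous abstinence from randomisation is a stated rule that does not fit people randomised before detoxification, and none of the three readings gives a usable, timing-neutral outcome. The first is close to uninformative, the second credits waiting time mostly to SPADe, and the third penalises SPADe.

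The size is known only under the second reading, and it depends on the assumed gaps and medians. With no true effect, apparent hazard ratios run from about 0.96 (7-day gap, 120-day median) to about 0.70 (14-day gap, 30-day median), and false-favour rates from about 3% to about 21% against a nominal 2.5%. The distortion is large when relapse is quick relative to the gap and small when it is slow. The documents do not establish a certain bias towards SPADe or a particular inflation of the error rate.

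**What to change.** **Change the origin.** In the Statistical analysis section, replace the randomisation origin with the length of the continuous abstinent spell from stopping alcohol, which the Outcome measures section already uses for time to relapse. Define the first day of that spell identically in both arms, score participants who never become abstinent as 0 days, and analyse everyone as randomised.

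**Report the delay.** Give the time from randomisation to detoxification by arm, as a result in its own right. Care pathways are already to be recorded for each participant.

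**Reconcile the two sections.** Time to relapse starts at stopping alcohol in Outcome measures and at the end of the intervention in Statistical analysis. Use one origin that exists in both arms.

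**If a summary anchored at randomisation is wanted,** use percentage of days abstinent within the observed Timeline Followback windows. Total abstinent days to 12 months cannot be computed: Table 1 collects the previous 90 days at 3, 6 and 12 months, which leaves roughly months 6 to 9 uncovered.

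**Cost.** This is mainly a change of wording, to be made before effect sizes are carried into the main trial. There are two drawbacks. Follow-up after detoxification will be slightly shorter in SPADe if detoxification is later there; censoring allows for this. For spells that run past month 6, an end date in about months 6 to 9 is interval-censored or rests on recall, and the analysis should say so.

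### Time to relapse is given two different starting points, and the one in the analysis section does not exist for the usual-care arm

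*Protocol article*

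**What the plan says.** The protocol article gives two origins for the same outcome.

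- Outcome measures: "time to relapse (from stopping alcohol to first day of alcohol use, also as defined by self-report". The clock starts when drinking stops, and the event is the first drink after that.
- Statistical analysis: "the time to relapse, as measured from the end of the intervention", to be analysed by Kaplan-Meier curve and log-rank test.

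The arm descriptions show what the second origin means. The section headed Intervention says: "The intervention provides structured group preparation (additional to usual care) with the aim of helping participants regain control over their drinking, prior to detoxification". The Abstract gives it to one arm only: "the intervention arm in which participants will receive structured group preparation before detoxification in addition to TAU". The other arm is described under Treatment as usual: "Usual detoxification/control comprises planning for detoxification, detoxification delivery and aftercare".

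The Statistical analysis section also commits the main analysis to all randomised clients by allocated arm. It names the estimation of parameters for the main trial's sample size as part of the main focus. Time to relapse is one of three outcomes from which the main trial's primary is to be chosen.

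**The concern.** A two-arm survival comparison needs one time zero, defined in the same way in both arms. The end of the intervention is not such a date. TAU participants receive no SPADe sessions, so the event never happens for them. SPADe participants reach it before their planned detoxification, and so in general before the abstinence whose duration is being measured.

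An analyst following the Statistical analysis section would have to invent a date for TAU, and any choice would leave the arms on different clocks. The resulting curve, hazard ratio and event rate would partly reflect the gap between clocks rather than relapse. Those are the quantities this feasibility study is meant to pass on to the main trial.

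**Working it through.** **Setting the sections side by side**

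| Question | Outcome measures | Statistical analysis |
|---|---|---|
| Clock starts | day drinking stops | end of the SPADe sessions |
| Exists in TAU? | yes, for anyone who stops | no |
| Position in the SPADe arm | start of abstinence | before planned detoxification |

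Nothing in the article reconciles the two or assigns TAU a substitute date. The inclusion criteria use the word intervention more loosely, for all candidates, but that use supplies no end date either.

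**Timing by design.** SPADe has six weekly sessions, so first to last spans (6 − 1) × 1 = 5 weeks, with detoxification afterwards. For TAU: "Service users enter detoxification at the first available opportunity (likely to be within 4 weeks from presentation". The wait between the last SPADe session and detoxification is not stated.

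**Figure to reproduce.** None. The article gives no event count, hazard ratio, power or sample-size calculation for time to relapse.

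**Illustration of the size.** All inputs below except the total of 50 are assumptions.

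- 25 per arm (50 / 2; the allocation ratio is not stated).
- True time T from stopping to relapse is exponential with rate ln 2 / median, the same in both arms, so there is no true effect.
- TAU clock: t = T, starting at stopping, as a stand-in for its missing date.
- SPADe clock: t = T + gap, because it starts at the end of the sessions. Drinking during the gap is not counted as relapse.
- Censoring at 40 weeks; 3,000 simulated trials per setting; two-sided log-rank test at 5%. Apparent hazard ratio (SPADe v TAU) = exp(mean of (O − E)/V).

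| Assumed median (weeks) | Gap 0: HR, rejection | Gap 2 weeks: HR, rejection | Gap 4 weeks: HR, rejection |
|---|---|---|---|
| 4 | 1.00, 6.4% | 0.68, 24.6% | 0.49, 60.0% |
| 8 | 1.01, 6.1% | 0.83, 10.0% | 0.69, 24.0% |
| 13 | 1.00, 5.4% | 0.88, 8.5% | 0.77, 14.0% |
| 26 | 0.99, 5.5% | 0.91, 6.3% | 0.85, 7.3% |

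With a common origin (gap 0) the hazard ratio is about 1 and rejection is near nominal. With a gap, the false rejections mostly favour SPADe. If drinking during the gap were counted as relapse, the bias would run the other way, because those SPADe participants would have events at or near time zero. That case follows by reasoning and was not simulated.

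**Can the dates be observed?** Table 1 gives the Timeline Followback (TLFB) as covering the previous 90 days at 3, 6 and 12 months. That is roughly months 0–3, 3–6 and 9–12. The last window opens at about 12 − 3 = 9 months, so months 6 to 9 lie outside every window.

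**The case against.** The best defence is that Outcome measures already gives an origin and an event usable in both arms, so this is one stray phrase. That largely stands. A reader might infer that time to relapse cannot be computed for half the trial. The documents do not support this: it is true only of the Statistical analysis wording taken alone, and removing that wording restores a workable definition.

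A reader might also infer that SPADe participants would all relapse at about day 0, being still drinking when the sessions end. That too is unsupported. Under Outcome measures, relapse can only follow stopping, so earlier drinking would not count. Moreover, the fifth session is about achieving abstinence, and some participants may stop before the sessions finish. The direction of the bias is therefore open.

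The simulated hazard ratios rest on a TAU clock that appears nowhere in the protocol. They show what a mismatch of a few weeks can do and do not forecast this trial's result.

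Finally, the analysis is mainly descriptive and tests are to be treated cautiously. Duration of continuous abstinence is measured from randomisation, and percentage of days abstinent needs no stopping date. This limits the harm to one of three candidate outcomes. It does not rescue that one, because caution about p-values does not correct an estimate built on mismatched clocks.

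**Conclusion.** The point holds. The two origins contradict each other, and the one attached to the analysis has no counterpart in TAU and by design precedes detoxification in SPADe. This rests on the article's own text and needs no assumption. Because both origins are stated, it is not a detail left to an unseen analysis plan. The size of any distortion cannot be derived from the documents. Under the stated assumptions, apparent hazard ratios run from 0.91 to 0.49 when the truth is 1.

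The stopping date is the better origin but is not complete by itself. It arises after randomisation, and anyone who never stops has none. A reader might conclude that the plan excludes such people and so breaks its commitment to analyse all randomised clients. The article does not say that; it is silent on how they are handled. The Background reports that an earlier version of the programme "reduced detox dropouts", which makes an arm difference in reaching abstinence plausible. That evidence comes from small naturalistic studies, however, and dropping out of detoxification is not the same as never stopping. The documents give no rate of stopping by arm, so no count of affected participants can be offered.

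**What to change.** 1. In Statistical analysis, delete the clause that measures time to relapse from the end of the intervention.
2. Use the Outcome measures origin identically in both arms: the first alcohol-free day after randomisation that begins the abstinence attempt, whether or not it was reached through detoxification. Tying the origin to the start of detoxification would leave anyone who stops without it with no clock.
3. Report by arm, for all randomised participants, the proportion who ever stop and the time from randomisation to stopping.
4. State in advance how those who never stop enter the analysis. Either score them as events at time 0, which keeps the all-randomised comparison, or label the time-to-relapse curve as conditional on stopping and descriptive. Both are defensible, and the text should name one.

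Cost: the change is to analysis wording and touches no treatment. Scoring at time 0 creates ties and turns the outcome into a composite; the conditional option means a two-part summary that is not a randomised comparison. First-drink dates in roughly months 6 to 9 are not covered by the 90-day TLFB at 12 months and would need interval censoring.
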